# ALternatives To prophylactic Antibiotics for the treatment of Recurrent urinary tract infection in women (ALTAR): study protocol for a multicentre, pragmatic, patient-randomised, non-inferiority trial

**DOI:** 10.1186/s13063-018-2998-4

**Published:** 2018-11-09

**Keywords:** Antibiotic resistance, Antibiotic prophylaxis, Economic evaluation, Qualitative research, Randomised controlled trial, RCT, Urinary tract infection, UTI

## Abstract

**Background:**

At least half of all adult women will experience infective cystitis (urinary tract infection: UTI) at least once in their life and many suffer from repeated episodes. Recurrent urinary tract infection (rUTI) in adult women is usually treated with long-term, low-dose antibiotics and current national and international guidelines recommend this as the ‘gold standard’ preventative treatment. Although they are reasonably effective, long-term antibiotics can result in bacteria becoming resistant not only to the prescribed antibiotic but to other antimicrobial agents. The problem of antimicrobial resistance is recognised as a global threat and the recent drive for antibiotic stewardship has emphasised the need for careful consideration prior to prescribing antibiotics. This has led clinicians and patients alike to explore potential non-antibiotic options for recurrent UTI prevention.

**Design /methods:**

This is a multicentre, pragmatic, patient-randomised, non-inferiority trial comparing a non-antibiotic preventative treatment for rUTI in women, methenamine hippurate, against the current standard of daily low-dose antibiotics. Women who require preventative treatment for rUTI are the target population. This group is comprised of those with a diagnosis of rUTI, defined as three episodes in 1 year or two episodes in 6 months, and those with a single severe infection requiring hospitalisation. Participants will be recruited from secondary care urology / urogynaecology departments in the UK following referral with rUTI. Participants will be followed up during a 12-month period of treatment and in the subsequent 6 months following completion of the prophylactic medication. Outcomes will be assessed from patient recorded symptoms, quality of life questionnaires and microbiological examination of urine and perineal swabs. The primary outcome is the incidence of symptomatic antibiotic-treated UTI self-reported by participants during the 12-month period of preventative treatment. Health economic outcomes will also be assessed to define the cost-effectiveness of both treatments. A qualitative study will be conducted in the first 8 months of the trial to explore with participants/non-participants’ and recruiting clinicians’ views on trial processes and identify potential barriers to recruitment, reasons for participating and non-participation and for dropping out of the study.

**Discussion:**

The study was commissioned and funded by the National Institute for Health Research (NIHR) and approved under the Medicines and Healthcare products Regulatory Agency (MHRA) notification scheme as a ‘Type A’ study.

**Trial registration:**

International Standard Randomised Controlled Trial Number (ISRCTN), registry number: ISRCTN70219762. Registered on 31 May 2016.

**Electronic supplementary material:**

The online version of this article (10.1186/s13063-018-2998-4) contains supplementary material, which is available to authorized users.

## Background

Recurrent urinary tract infection (rUTI) in adult women is one of the most common infections in humans. Bacteria from the vagina or faecal matter inoculate the periurethral area, then the bladder, causing symptoms of cystitis. The lifetime risk of a urinary tract infection (UTI) is around 40% in adult women and the incidence peaks in the third and ninth decades. The annual incidence of a single UTI is 3% [1] with up to 44% of these women experiencing recurrence within 1 year [2]. This equates to an affected population of over 300,000 women in 1 year in the UK [3].

The prophylactic treatment of rUTI with extended courses of low-dose antimicrobial therapy is standard practice and a meta-analysis from the Cochrane Collaboration shows that this reduces recurrence rate by up to 80% [4]. However, antibiotics are the main driving force in the development of antibiotic resistance and can lead to resistance not only of the causative microorganisms but also of the commensal flora [5]. Prudent antibiotic prescribing (stewardship) is one of the cornerstones of UK and international strategies to prevent antimicrobial resistance [6, 7] and recent guidelines have identified that ‘repeated/prolonged treatment with antibiotics’ is contributory to the development of this serious health problem [8]. Alternative, non-antibiotic treatments for the prevention of rUTI have the potential to improve public health by minimising the development of antimicrobial resistance in bowel reservoirs and well-designed trials are needed to demonstrate their effectiveness.

## The current body of evidence and the contribution of this study

Prophylactic antibiotics constitute the current standard of care for the preventative treatment of rUTIs and are recommended for this use by both UK and European guidelines [8, 9] .The largest meta-analysis examining the efficacy of prophylactic antibiotics reveals an 85% reduction in symptomatic UTI over placebo (RR 0.15, 95% CI 0.08 to 0.28) [4]. This meta-analysis included 19 studies with data from 1120 women. The authors concluded that continuous antibiotic prophylaxis for 6–12 months reduced the rate of UTI during prophylaxis when compared to placebo. There were, however, more adverse events (AEs) in the antibiotic group and these included vaginal and oral candidiasis and gastrointestinal symptoms. The observation that following treatment the rate of symptomatic UTI returned to similar levels in both women taking prophylactic antibiotics and those receiving placebo comes from only two studies. This does, however, suggest that the benefits of antibiotics are not sustained following cessation of treatment.

Methenamine hippurate has been the subject of a meta-analysis from the Cochrane Collaboration [10] and this included 13 studies comprising data from 2043 patients. The reduction in UTIs was of the order of 76% (RR 0.24, 95% CI 0.07 to 0.89). The authors did however comment that the quality of the included studies was mixed and that pooled estimates for the major outcome measures were not interpretable because of underlying heterogeneity. Nevertheless, they were able to assert that methenamine hippurate may be effective for preventing UTI in patients without renal tract abnormalities, particularly when used for short-term prophylaxis. The rate of AEs was low, but poorly described. The need for large, well-conducted clinical trials to clarify the effectiveness of methenamine hippurate in the setting of prevention of UTIs was highlighted.

Although continuous antibiotic treatment has been shown to prevent rUTIs [4] previous randomised trials have demonstrated an associated threefold increase in the incidence of antimicrobial resistance compared with placebo [11]. Several studies have confirmed the emergence of resistant organisms in the faecal reservoir and urine of women who take prolonged antibiotics [11, 12]. The resistance pattern observed was not confined to the prescribed antibiotic but to a range of other antibiotic agents commonly used to treat symptomatic UTI [1]. Furthermore the detection of resistant microorganisms can occur after just a few weeks of prophylactic antibiotic therapy [11]. The use of effective non-antibiotic UTI prevention strategies will reduce risk to patients of emergence of resistant organisms and subsequent difficult-to-treat clinical infection with these bacteria. The incidence of antimicrobial multi-resistance within post-menopausal women suffering from rUTI is around 25% and was shown to rise to more than 80% following prolonged antibiotics [5].

The advisability of using non-antibiotic preventative treatments for rUTI has been highlighted by recent UK, European and US guidelines to reduce the ‘collateral damage’ of antibiotic use by minimising risk of resistance development [6]. Policy-makers in the UK and Internationally have included antibiotic avoidance and prudent antibiotic prescribing as key components of action plans and strategies to reduce antimicrobial resistance [13, 14]. A well-designed research study providing robust evidence of at least equivalent effectiveness of non-antibiotic treatment is needed to further inform guideline-writers and policy-makers and allow recommendation of alternative treatments avoiding prolonged antibiotic use.

In addition to the problem of antimicrobial resistance within an individual’s faecal reservoir there is a wider public health concern regarding the continued emergence of healthcare-associated infections (HAI) initially focussed on methicillin resistant *Staphylococcus aureus* (MRSA) and *Clostridium difficile* infection (CDI) and more recently other types of multi-resistant organisms including those producing extended-spectrum beta lactamases (ESBL). The predominant uropathogen, *Escherichia coli (E. coli)*, is the subject of a recent article identifying the overuse of non-prescription antibiotics in Asia as a potential causative factor for the development of a new mechanism of ESBL antibiotic resistance detected in the UK [15]. Limiting the use of broad-spectrum antibiotics is a key measure in addressing this problem, and has been the driver for recent UK guideline updates [8]. The development of antimicrobial stewardship programmes which encourage prudent antibiotic prescribing has already been shown to reduce antibiotic use and consequently the incidence of HAI which until recently was increasing [16, 17]. Avoidance of antibiotic administration, where possible, is believed to be the single most important factor leading to the observed decline in HAI in Scotland [17]. A positive result from our study will further encourage avoidance of antibiotic prescription by providing high-level evidence of efficacious non-antibiotic alternatives reducing the chance of emergence of multi-resistant UTIs.

Our study will address the question of whether the use of the urinary antiseptic methenamine hippurate (a non-antibiotic preventative treatment) results in an equivalent reduction in rate of symptomatic UTIs compared to prophylactic antibiotic therapy in women suffering from rUTI. In addition, we will assess the longer-term effectiveness of these two treatments by following up all participants for 6 months after treatment. We will also evaluate both treatments in terms of their cost-effectiveness and effect on overall quality of life (QoL). Furthermore, secondary outcomes will assess whether use of this alternative preventative treatment reduces the development of antimicrobial resistance within uropathogens that is associated with antibiotic use including the main pathogen *E. coli*. Using health economic analysis, we aim to value this benefit to women suffering rUTI and to the wider NHS.

## Why this research is needed now

A recent meta-analysis reviewed the evidence for non-antibiotic treatments as prophylaxis against rUTI but the results were disappointing, mainly due to paucity of evidence [18]. One of the conclusions in this report was that ‘Although sometimes statistically significant, pooled findings for the other (non-antibiotic) interventions should be considered tentative until corroborated by more research’. It would appear that one of the barriers to clinicians recommending non-antibiotic alternatives for the treatment of rUTI is the lack of currently available clinical evidence. The campaign for antibiotic stewardship and more prudent prescribing of antibiotic agents can only be strengthened by further work exploring effectiveness of non-antibiotic alternatives. A further conclusion from this meta-analysis was that ‘Large head-to-head trials should be performed to optimally inform clinical decision-making’.

The most recent guideline published on the subject of UTI is the 2012 Scottish Intercollegiate Guideline Network (SIGN) guideline 88 [8] which forcibly illustrates why our proposed study is essential and needed promptly. The literature review carried out prior to formulation of this document identified ‘considerable evidence of practice variation’ and variation in ‘initiation of antibiotic treatment’ for UTI. In addition, one of the constant themes in this report is the need to avoid ‘unnecessary antibiotic prescribing’ which is associated with ‘clinical adverse events including *Clostridium difficile* infection (CDI) or methicillin-resistant *Staphylococcus aureus* (MRSA) infection, and the development of antibiotic-resistant (*E. coli*) UTIs’. The UK antimicrobial resistance strategy and action plan [6] states that ‘the increasing prevalence of antimicrobial resistant micro-organisms is causing international concern’ and identifies that ‘the emergence of resistance represents adaptive selection by micro-organisms which is an inevitable result of therapeutic use of antimicrobial agents’. This document reflects an urgent need for prudent antibiotic use as one of three key elements of the strategy to control antibiotic resistance. The ALTAR study aims to provide high-level contemporary evidence of the relative effectiveness of a non-antibiotic UTI prevention treatment compared to the standard treatment of prolonged, low-dose antibiotics within a UK population of women with rUTI in a routine NHS care setting.

## Design/methods

The ALTAR trial is a robust, pragmatically designed trial to evaluate the clinical benefit and cost-effectiveness of the best candidate alternative treatment for the prevention of rUTI, the urinary antiseptic methenamine hippurate compared to the standard treatment of low-dose prophylactic antimicrobial therapy. Outside of the trial medication, both groups will receive usual care and any breakthrough UTI will be treated by discrete courses of antibiotic treatment.

The null hypothesis being tested is that the non-antibiotic treatment (methenamine hippurate) is inferior to the standard treatment of an extended course of prophylactic antibiotic for the prevention of rUTI in women and less cost-effective to the NHS. The alternative hypothesis is that methenamine hippurate is as good at preventing UTI and is as cost-effective as antibiotic prophylaxis. We have chosen to investigate the possible non-inferiority of methenamine hippurate in order to clarify an alternative treatment choice to antibiotics in treating rUTIs, which may prevent increases in antibiotic-resistant strains of infection.

Estimates of prevalence, effectiveness and harms from Cochrane reviews have informed the power calculation conservatively based on what we, guided by a patient panel, considered to be a minimum threshold difference that would drive patient and clinician acceptability together with change of practice prompted by inclusion of trial results in future meta-analyses and guidance for management of rUTI in the NHS and internationally.

The anticipated trial flow for participants is shown in Fig. 1  and the trial schedule of procedures is shown in Table 1.

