### Sample size calculation

The clinical trial has a planned recruitment target of 240 patients, 120 in each of the treatment arms. If there is an actual difference of 0.6 episodes (in favour of treatment with antibiotics), then two groups of 87 patients are required to be 90% sure that the lower limit of a one-sided 95% confidence interval (or equivalently a 90% two-sided confidence interval) will be above the non-inferiority limit of one UTI episode assuming a standard deviation of 0.9 episodes per year. Total sample size assuming two groups and an attrition rate of 25% = 232, rounded up to 240.

We have discussed extensively the relative merits of non-inferiority against superiority comparison and believe the key issue is that an orally administered urinary antiseptic would be acceptable to the patient group provided that their effectiveness for UTI prevention is no worse than antibiotic prophylaxis and that the burden of adverse effects is similar or better. There is also the key added potential benefit of reduced rates of resistant organisms and subsequent collateral harm to the individual and the community. The sample size calculation is based on the following assumptions:Semi-structured interviews with a patient panel of 12 women identified that any reduction in UTI episodes even by one per year would be deemed worthwhile. Therefore, we have set the minimum clinically important difference between the treatment arms of one UTI per 12 months as our non-inferiority marginThe two existing meta-analyses of studies examining prophylactic antibiotics [6] and methenamine hippurate [7] have quoted mean relative risk of UTI vs placebo of 0.15 and 0.24, respectively. Using these values and data from a local audit (unpublished, *n* = 200) suggesting that the average number of UTI episodes per year in this patient group is 6.5, we have estimated that the difference in number of episodes per year between prophylactic antibiotics and methenamine hippurate to be 0.6 episodes (in favour of antibiotics)The standard deviation of episodes of UTI per year is taken from the placebo groups in the studies included in the Cochrane meta-analyses [4, 10] and has been conservatively estimated at 0.9 episodes per yearThe type-1 error rate for a two group comparison is set at 5%, thus the calculation of a one-sided 95% confidence interval (or a two-sided 90% confidence interval)The attrition rate of participants in this study has been conservatively estimated at 25%

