### Statistical analysis

The main analysis will comprise a comparison of patients randomised to antiseptic with patients randomised to antibiotic (‘intention to treat’).The primary clinical outcome is the occurrence of symptomatic UTI during the 12-month period of treatment. Our hypothesis is that treatment with antiseptic is not inferior to treatment with antibiotic. When considering an inferiority limit the variable that patients most readily relate to is the number of episodes experienced during treatment. The inferiority limit adopted for this study will be one episode per year. A 90% confidence interval for the difference between groups (antibiotic minus antiseptic) will be calculated using a resampling (bootstrap) procedure. Provided that the lower 90% confidence limit is greater than the pre-specified non-inferiority limit (here − 1 for this definition of difference as a higher (worse) value in the antiseptic group would result in a negative difference), we will infer that treatment with antiseptic is not inferior to treatment with antibiotic.

A secondary analysis of the primary outcome will involve the modelling of the number of episodes of UTI using a negative binomial regression model with differences between centre included as a random effect and a binary indicator of previous annual frequency of UTI at baseline (more than four episodes vs four or less episodes) and menopausal status (pre-menopausal vs menopausal/post-menopausal) will be included as fixed effects. This will yield an estimate of the incidence rate ratio. A binary indicator of at least one patient-reported or clinician-recorded symptom of UTI will be analysed using the same approach but with a binomial error structure. The same methods will be used to analyse the relative frequency of episodes of UTI during the 6-month post-treatment period as a secondary outcome.

Analysis of the secondary outcomes will follow a broadly similar strategy although non-inferiority will not be assessed as this is only relevant for the pre-specified primary outcome. Incidence or occurrence type outcomes will be analysed in a manner analogous to that previously described for the primary outcome. Patient satisfaction will be compared between arms using an analysis of variance/covariance approach adjusting for stratification variables and other predefined baseline covariates. Health-related QoL will be analysed as part of the health economics analysis.

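### The SD of 0.9 is too small for the UTI rates that produce the 0.6 difference; at the planning point, power is about 76–80%, not 90%

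*Protocol article*

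**What the plan says.** The Sample size calculation section plans on a true deficit for methenamine: "If there is an actual difference of 0.6 episodes (in favour of treatment with antibiotics". It concludes that "two groups of 87 patients are required to be 90% sure that the lower limit of a one-sided 95% confidence interval" "will be above the non-inferiority limit of one UTI episode assuming a standard deviation of 0.9 episodes per year". Allowing for 25% attrition gives 232, rounded up to 240, or 120 per arm.

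The same section explains the inputs:

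- The 0.6 is obtained by applying relative risks against placebo of 0.15 (antibiotics) and 0.24 (methenamine) to an average of 6.5 episodes a year from a local audit.
- On the SD: "The standard deviation of episodes of UTI per year is taken from the placebo groups in the studies included in the Cochrane meta-analyses". The section calls the resulting 0.9 a conservative estimate.
- The margin is one episode per year and the type 1 error rate is 5% one-sided.

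The Design/methods section also uses the word conservatively: "Estimates of prevalence, effectiveness and harms from Cochrane reviews have informed the power calculation conservatively". That sentence goes on to the patient-panel threshold difference and mentions no SD.

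The Statistical analysis section bases the primary comparison on a bootstrap 90% interval for the difference in episodes. A secondary analysis involves "modelling of the number of episodes of UTI using a negative binomial regression model".

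**The concern.** The outcome is a count of episodes per woman over 12 months, so its mean and variance are linked. The plan fixes both means when it derives the 0.6, and then takes the SD from a different source. A variance of 0.81 in both arms is below the Poisson variance for either mean, so the calculation implicitly assumes counts less variable than Poisson. Yet the plan expects women to differ: it stratifies randomisation on prior UTI frequency and fits a model that allows extra-Poisson variation.

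What is at stake is how an inconclusive result would be read. If the interval crosses −1, a reader who trusts the stated power will think that outcome had a 10% chance at the planned difference. Under the plan's own rates, with Poisson variance, the chance is about 1 in 5 to 1 in 4 at 87–90 evaluable women per arm.

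**Working it through.** **Inputs.** From the Sample size calculation section: margin 1, true difference 0.6, SD 0.9, one-sided α 5%, power 90%, untreated rate 6.5 a year, relative risks 0.15 and 0.24, attrition 25%. The added assumption is Poisson variance (variance = mean).

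**1. Reproduce the plan.**
n per arm = 2 × (1.645 + 1.282)² × 0.9² / (1 − 0.6)² = 2 × 8.57 × 0.81 / 0.16 ≈ 86.7, so 87.
Total = 174 / 0.75 = 232. Power at 87 per arm is 90.1% (about 92% with the unrounded difference of 0.585). The stated figures follow exactly from SD 0.9.

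**2. Means implied by the 0.6.**
Antibiotic: 6.5 × 0.15 = 0.975. Methenamine: 6.5 × 0.24 = 1.56. Difference: 0.585, rounded to 0.6.

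**3. Poisson SDs at those means.**
√0.975 = 0.99 and √1.56 = 1.25. Root-mean-square: √((0.975 + 1.56)/2) = √1.2675 = 1.13. The plan's variance of 0.81 is 83% and 52% of the two Poisson variances.

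**4. Power with those variances.**
Power = Φ((1 − d)/√((0.975 + 1.56)/n) − 1.645).
For n = 87 and d = 0.6: SE = √(2.535/87) = 0.1707; 0.4/0.1707 − 1.645 = 0.70; Φ = 75.8%.

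| Evaluable per arm | d = 0.6 | d = 0.585 |
|---|---|---|
| 87 | 75.8% | 78.4% |
| 90 (120 less 25%) | 77.0% | 79.6% |
| 120 (no attrition) | 86.6% | 88.7% |

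The chance of missing non-inferiority is therefore 20–24% at 87–90 per arm and 11–13% at 120. For scale only, 90% power would need 136 evaluable per arm (d = 0.6) or 127 (d = 0.585).

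**5. Overdispersion (illustrative).** Variance = mean + k × mean². The document gives no k, so these values are assumptions.

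| k | Root-mean-square SD | Power at 87 per arm (d = 0.6 to 0.585) |
|---|---|---|
| 0.25 | 1.30 | 65–68% |
| 0.5 | 1.45 | 57–59% |
| 1 | 1.72 | 46–48% |

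**6. Smaller true differences.** With the antibiotic mean kept at 0.975, Poisson variance and 87 per arm, d = 0.5 gives SE = √((0.975 + 1.475)/87) = 0.168 and 0.5/0.168 − 1.645 ≈ 1.33, so power is about 91%. At d = 0.4 it is about 98%.

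**The case against.** **The calculation contains real caution.** It does not assume equal efficacy. It powers the trial at a deficit that is already 60% of the margin, and step 6 shows that a modestly smaller deficit restores 90%. This stands. The shortfall belongs to the planning point of 0.585–0.6, which is also the point at which the document states its 90%.

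**Poisson variance is a benchmark, not a mathematical minimum.** A woman under treatment for one UTI cannot start another, which reduces the variance. This also stands, but it does not rescue 0.9. Assume identical women and a period after each episode in which no new one can begin. With 14 days the SDs are about 0.96 and 1.18, and power at 87 per arm is about 79–82%. With 28 days they are about 0.92 and 1.11, and power is about 83–85%. Both SDs still exceed 0.9 before any variation between women is added.

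**More than 90 per arm may be evaluable.** The analysis is by intention to treat, women who stop treatment stay on study, and primary care records are reviewed. That is fair, but even 120 per arm gives 87–89%.

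Three stronger readings are tempting, and the document does not support them:

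- *That 0.9 is refuted by the SD expected at the untreated rate* (√6.5 = 2.55). The 6.5 comes from a local audit and the SD from placebo groups in other studies. Those groups' event rates are not given, so the comparison mixes sources.
- *That the plan itself assumes overdispersion.* The negative binomial model is secondary. It allows for extra variation but quantifies none, and Poisson is its limiting case.
- *That the Design/methods sentence is also wrong.* There the word conservatively can attach to the threshold difference. Only the sample size section applies it to the SD.

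**Conclusion.** The point holds as an inconsistency between inputs. The SD of 0.9 is below the Poisson SD in each arm at the rates that generate the 0.6, so it is optimistic rather than conservative. At the planned difference, power is about 76–80% with 87–90 evaluable women per arm and 87–89% with no attrition, against a stated 90%.

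This rests on three things: the plan's use of relative risks as multipliers of the yearly rate, counts at least roughly Poisson in spread, and a true difference of 0.585–0.6. The overdispersed figures are illustrations, because k is assumed.

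A reader might infer that the sample size was miscalculated or that the primary analysis is compromised. Neither follows. The figures 87 and 232 are correct for SD 0.9, and rounding to 240 is harmless. The bootstrap interval takes its width from the observed data; 0.9 never enters it, and the margin, error rate and decision rule are untouched. The correction should be made because readers will use the stated power to interpret an inconclusive interval, but it is a matter of reporting the design properly.

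**What to change.** Change only the Sample size calculation section:

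- Keep 87, 232 and 240 as the basis on which the trial was sized. Simply substituting 1.13 for 0.9 would leave 87 without a derivation.
- Remove the description of the SD as conservative, and state that 0.9 is below the Poisson SD implied by the assumed rates (0.99 and 1.25).
- Restate the power at the planned difference as about 76–80% with 87–90 evaluable per arm and 87–89% with no attrition. Add an overdispersion sensitivity range whose k values are labelled as assumptions.
- Add that power is about 90% or more, under Poisson variance, if the true difference is 0.5 or less.

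Leave the Design/methods sentence, the sample size, the margin and the analysis as they are. The Trial status section reports that recruitment has reached target, and no added patients are proposed. The cost is a few sentences and a less favourable stated power.
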